## Abstract

**Introduction:**

The confidence of young people diagnosed with psychosis is often low. Positive self-beliefs may be few and negative self-beliefs many. A sense of defeat and failure is common. Young people often withdraw from many aspects of everyday life. Psychological well-being is lowered. Psychological techniques can improve self-confidence, but a shortage of therapists means that very few patients ever receive such help. Virtual reality (VR) offers a potential route out of this impasse. By including a virtual coach, treatment can be automated. As such, delivery of effective therapy is no longer reliant on the availability of therapists. With young people with lived experience, we have developed a staff-assisted automated VR therapy to improve positive self-beliefs (Phoenix). The treatment is based on established cognitive behavioural therapy and positive psychology techniques. A case series indicates that this approach may lead to large improvements in positive self-beliefs and psychological well-being. We now aim to conduct the first randomised controlled evaluation of Phoenix VR.

**Methods and analysis:**

80 patients with psychosis, aged between 16 and 30 years old and with low levels of positive self-beliefs, will be recruited from National Health Service (NHS) secondary care services. They will be randomised (1:1) to the Phoenix VR self-confidence therapy added to treatment as usual or treatment as usual. Assessments will be conducted at 0, 6 (post-treatment) and 12 weeks by a researcher blind to allocation. The primary outcome is positive self-beliefs at 6 weeks rated with the Oxford Positive Self Scale. The secondary outcomes are psychiatric symptoms, activity levels and quality of life. All main analyses will be intention to treat.

**Ethics and dissemination:**

The trial has received ethical approval from the NHS Health Research Authority (22/LO/0273). A key output will be a high-quality VR treatment for patients to improve self-confidence and psychological well-being.

**Trial registration number:**

ISRCTN10250113.

STRENGTHS AND LIMITATIONS OF THIS STUDYThis is a randomised controlled trial that will provide an estimate of the treatment effect of the addition of the Phoenix virtual reality self-confidence therapy to standard care.The primary outcome is a new self-report measure of positive self-beliefs that is strongly associated with psychological well-being.The secondary outcomes cover a wide range of psychiatric, functioning and quality-of-life domains.The trial will not be able to determine the components of the intervention that lead to any clinical benefits.The trial is only powered to detect at least moderate effect size improvements in positive self-beliefs.

## Introduction

Patients diagnosed with schizophrenia (and related non-affective psychosis) have often experienced difficult lives;^1^ may be coping with distressing psychotic experiences, low mood and anxiety;^2^ and can suffer stigma both from themselves and others.^3^ Patients typically view themselves negatively, believe that they are inferior to others and can be overly self-critical.^4^ Positive self-views that could counteract such beliefs are often not formed, consolidated or accessible.^5^ The negative self-views, and limited levels of positive self-views, can exacerbate negative affect and psychotic experiences.^6^ An end result is that often individuals withdraw from many aspects of their lives.^7^ They may become inactive and isolated,^8^ with further negative consequences for mental and physical health. Overall, levels of psychological well-being are often very low in patients with psychosis.^9^ We set out to develop a potentially scalable intervention that can build up positive self-beliefs and hence psychological well-being. Our aim is to arrest this downward spiral as soon as possible by focusing on patients at the early stages of psychosis.

Psychological techniques delivered in face-to-face therapy, and drawing on cognitive behavioural therapy and positive psychology,^10–12^ can improve self-confidence. In a pilot randomised controlled trial of six sessions of face-to-face therapy with patients with current persecutory delusions in the context of a diagnosis of psychosis, we showed that it is possible to achieve large improvements in positive beliefs about the self, social comparison and psychological well-being.^13^ However, very few patients receive such psychological therapy. There is a shortage of psychological therapists for patients with schizophrenia. Even fewer therapists have the time to take patients into real-world situations where the most important work is conducted: building up self-confidence through direct experience. Our potential solution is to use immersive technology. Virtual reality (VR) therapy involves wearing a headset and interacting with computer-generated simulations in carefully selected scenarios. The significant advantages of VR are that: it allows users repeatedly to experience therapeutically beneficial simulations; learning has been demonstrated to transfer from the virtual environment to the real world;^14–16^ the therapy can be made compelling and entertaining; and treatment can be automated within VR, removing reliance on the availability of therapists.^17^

In a user-centred design process with young people with lived experience of psychosis we designed a VR therapy to improve positive self-beliefs (Phoenix VR) (Rosebrock *et al*, submitted). The treatment built on our face-to-face therapy. The VR therapy had high usability ratings. The treatment is programmed to run on a stand-alone VR consumer headset that can be left with patients. A staff member then has up to six sessions with the patient to introduce the VR therapy and help the person apply the learning to the real world. Patients can have these sessions at home or in the clinic. An initial proof of concept case series test of Phoenix VR therapy was conducted.^18^ Twelve young patients diagnosed with psychosis received Phoenix. There were large improvements in positive beliefs about the self (d=3.0) and psychological well-being (d=1.5) after the intervention. However, this evaluation did not include a control group. As such, improvements could have been a consequence of natural recovery. A randomised controlled evaluation of Phoenix VR self-confidence therapy is now required.

### Aims and hypotheses

Our primary research question is: Does Phoenix VR self-confidence therapy added to treatment as usual, compared with treatment as usual alone, lead to a post-treatment improvement in levels of positive self-beliefs for patients at the early stages of psychosis attending NHS mental health services?

Our primary hypothesis is that:

Compared with treatment as usual, Phoenix VR self-confidence therapy added to treatment as usual will improve levels of positive self-beliefs (end of treatment).

Our secondary hypotheses are as follows:

Compared with treatment as usual, Phoenix VR self-confidence therapy added to treatment as usual will improve social comparison and psychological well-being (end of treatment).Compared with treatment as usual, Phoenix VR self-confidence therapy added to treatment as usual will reduce depression, negative self-beliefs, hopelessness, anhedonia, anxiety, and paranoia and increase perceptions of recovery, meaningful activity and quality of life (end of treatment).Treatment effects will be maintained at follow-up (3 months).

We will also collect data on satisfaction, side effects and health economic variables.

## Methods and analysis

### Trial design and flow chart

The design is a parallel group, superiority, single-blind, randomised controlled trial to test the effects of Phoenix VR therapy when added to usual care. The trial will be run from a single centre, with up to four NHS mental health trusts participating (Oxford Health NHS Foundation Trust; Berkshire Healthcare NHS Foundation Trust; Northamptonshire Healthcare NHS Foundation Trust; Central and North West London NHS Foundation Trust (Milton Keynes)). Treatment as usual will be measured but remain unchanged in both groups. Assessments will be conducted at 0, 6 and 12 weeks. Assessments will be conducted in person or online by research assistants blind to group allocation. A summary of the trial design can be seen in figure 1. The trial is prospectively registered with the ISRCTN registry: ISRCTN10250113. The University of Oxford is the trial sponsor. There is a data monitoring and ethics committee (DMEC).

**Figure 1 F1:**
[figure not shown]
Trial flow diagram. VR, virtual reality; TAU, treatment as usual.

#### Randomisation, blinding and code-breaking

Participants will be randomised after completing the baseline assessment and allocated to one of the trial arms using a 1:1 allocation ratio. Randomisation will be carried out by a validated online system provided by Sealed Envelope (www.sealedenvelope.com) and using a permuted blocks algorithm, with randomly varying block size.

The research assessors will be blinded to group allocation, but the patients and staff member present will not (they cannot be blinded to whether psychological intervention is delivered or received). If an allocation is revealed between assessment sessions, this will be logged by the trial coordinator and reblinding will occur using another assessor.

#### Participants

Participants will be NHS patients diagnosed with non-affective psychosis, with low positive self-beliefs, and aged 16–30 years old. Participants will be recruited principally by seeking referrals to the trial from the relevant clinical teams in the participating mental health trusts (early intervention services, adult community mental health teams and inpatient units). Patients interested in taking part will then be approached by the research team with the approval of the clinical team, given information about the trial and screening conducted. All suitable patients will be given at least 24 hours to consider taking part in the trial. Our Lived Experience Advisory Panel (LEAP) has emphasised the importance of patients being able to self-initiate referral. This minimises the chance that particular patients miss out on trials because they are overlooked by clinical teams or their clinician was absent from a referral meeting. However, in all instances, we will seek to confirm that a member of the clinical team gives approval for a patient to enter the trial and to complete the necessary screening of eligibility and risk status. Written informed consent will be obtained from all participants.

The inclusion criteria are: Participant is willing and able to give informed consent for participation in the trial; aged between 16 years and 30 years old; attending NHS mental health services for treatment of psychosis; primary clinical diagnosis of non-affective psychosis (schizophrenia, schizoaffective disorder, delusional disorder or psychosis NOS); low levels of positive self-beliefs indicated by a score of 50 or lower on the Oxford Positive Self Scale;^19^ stable medication for at least 1 month and no planned significant changes at the outset of participation.

The exclusion criteria are: a primary diagnosis of another mental health condition (eg, substance use disorder) that would be the first clinical priority to treat; current engagement in any other intensive individual psychological therapy; in forensic settings or psychiatric intensive care unit (PICU); command of spoken English inadequate for engaging in the VR therapy; photosensitive epilepsy or significant visual, auditory or balance impairment that would make use of VR inappropriate; significant learning difficulties that would prevent the completion of assessments. A participant may also be excluded if there is another factor (eg, current active suicidal plans) which, in the judgement of the investigator, would preclude the participant from providing informed consent or from safely engaging with the trial procedures. Reason for exclusions will be recorded.

#### Assessments

The primary outcome is the total score on the Oxford Positive Self Scale.^19^ This is a 24-item self-report scale assessing four types of positive self-belief: mastery, strength, enjoyment and character. It was developed with a representative sample of 2500 members of the UK population, with further validation in another three thousand individuals. It has a high correlation with psychological well-being (r=0.79). The psychometrics of the scale are excellent, including internal consistency (omega coefficient=0.92).

Secondary outcomes are assessments of social comparison, specifically the Social Comparison Scale,^20^ and psychological well-being, using the Warwick-Edinburgh Well-being Scale.^21^ Negative and positive self-beliefs will also be assessed with the Brief Core Schema Scale-Negative and Positive Self subscales^5^ and the Everyday Confidence Scale.^22^ Depression will be assessed with the Patient Health Questionnaire-9,^23^ hopelessness with the Beck Hopelessness Scale,^24^ anhedonia with the Temporal Experience of Pleasure Scale-anticipatory pleasure,^25^ anxiety with the GAD-7 (Generalised Anxiety Disorder Assessment)^26^ and paranoia with the Revised Green *et al* Paranoid Thoughts Scale.^27^ We will also assess perceptions of recovery with the Questionnaire of Process of Recovery,^28^ meaningful activity with a time budget,^29^ and quality of life with the EQ-5D-5L (EuroQol)^30^ and the ReQol.^31^ Service use data will be collected with the Modified Client Service Receipt Inventory.^32^ For patients in the Phoenix VR therapy arm, the staff member will collect end-of-treatment assessments of satisfaction, using the Modified Client Satisfaction Questionnaire,^33 34^ and side effects, via the Oxford-VR Side Effects Scale.^35^ A summary of the measures is provided in table 1.

**Table 1 T1:** Summary of objectives and assessment measures

	Objectives	Outcome measures
Primary	Test whether the VR treatment leads to improvement in positive self-beliefs.	Oxford Positive Self Scale
Secondary	Test whether the VR therapy improves social comparison and psychological well-being.	Social Comparison Scale, Warwick-Edinburgh Well-being Scale
	Test whether the VR therapy leads to reductions in depression, negative self-beliefs, everyday self-confidence, hopelessness, anhedonia, anxiety, and paranoia and increases in perceptions of recovery, meaningful activity and quality of life.	Patient Health Questionnaire-9, Brief Core Schema Scale, Everyday Confidence Scale, Beck Hopelessness Scale, Temporal Experience of Pleasure Scale, Generalised Anxiety Disorder Assessment (GAD-7), Revised Green *et al* Paranoid Thoughts Scale, Questionnaire of Process of Recovery, time budget, EQ-5D-5L (EuroQol), ReQol.
	Assess patient satisfaction with the VR therapy.	Modified version of the Client Satisfaction Questionnaire.
	Assess side effects of the VR therapy	Oxford-VR Side Effects Scale

VR, virtual reality.

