#### The VR psychological treatment

The treatment being tested is Phoenix VR self-confidence therapy, which is a VR application recommended for adults (16+) attending psychosis services who have low levels of positive self-beliefs. This software is intended to increase positive self-beliefs. The treatment was designed by our team at the University of Oxford, with young people with lived experience taking part in the design process. The treatment was programmed by the University of Oxford. Phoenix is a UKCA marked, class I medical device (standalone software as a medical device). The Phoenix software application is composed of a set of virtual environments, including different scenes created using three-dimensional (3D) models, ambient audio and 3D virtual characters, with animations and speech. The environments are driven by source code which handles the logic of the programme, the behaviour of the computer characters, as well as the user interaction and data storage. The software is built using Unity (Unity Technologies). Unity acts as a render engine, displaying the virtual environments to the user through the headset. The application runs through the Unity software application on a Meta Quest 2 VR Headset.

The primary treatment goal is to help young people who have been given a diagnosis of schizophrenia (or related condition) to increase their psychological well-being by building up positive self-beliefs. Patients can keep the headset for 6 weeks in order to use Phoenix on their own. The treatment is supported by a staff member over six sessions. In the first meeting, the staff member introduces Phoenix and helps the person try it out. The staff member also helps the person set real-world goals and between-session tasks to improve confidence and reviews progress. VR does not need to be used in the subsequent in-person meetings since the patient is able to use it at home but most sessions to date have included approximately twenty minutes within VR. Phoenix is used to spark positive self-beliefs that are then consolidated via real-world activities.

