#### Adverse events

A trial standard operational procedure has been written for adverse events. We will record the occurrence of any serious adverse events (SAE) reported to us and also check each patient’s medical notes at the end of their participation in the trial. An adverse event is defined by the ISO14155:2011 guidelines for medical device trials as serious if it: (A) results in death, (B) is a life-threatening illness or injury, (C) requires hospitalisation or prolongation of existing hospitalisation, (D) results in persistent or significant disability or incapacity, (E) medical or surgical intervention is required to prevent any of the above, (F) leads to foetal distress, foetal death or consists of a congenital anomaly or birth defect or (G) is otherwise considered medically significant by the investigator.

Life-threatening in the definition of an SAE refers to an event in which the subject was at risk of death at the time of the event; it does not refer to an event that hypothetically might have caused death if it were more severe. A planned hospitalisation for a pre-existing condition, without a serious deterioration in health, is not considered to be an SAE.

The sorts of SAEs that can typically happen to this participant group include: deaths, suicide attempts, serious violent incidents and admissions to hospital. SAEs are recorded using an SAE report form. The relationship between the investigational medical device or other research procedure and the occurrence of each SAE will be assessed and categorised. The investigators will use clinical judgement to determine the relationship (including whether the patient reports a link to the study). Alternative causes, such as natural history of the participant’s underlying condition, concomitant therapy, other risk factors, etc, will be considered. The study team will make an initial assessment of whether the SAE is potentially related to the device or trial procedures and report to the regulatory authorities within the appropriate timescales. The decision about relatedness will be reviewed by the DMEC chair in the first instance.

We will also record adverse events that are not serious. This would include any adverse device effects from the VR treatment, including those resulting from insufficient or inadequate instructions for use, deployment, installation or operation, or any malfunction of the software. It also includes any event resulting from user error or intentional misuse.

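### Satisfaction and VR side-effect ratings are collected by the unblinded staff member who supports the therapy, so these Phoenix-arm results may lean favourable

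*Protocol article*

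**What the plan says.** The rule is in the Assessments section of the protocol article, for the Phoenix arm only: "the staff member will collect end-of-treatment assessments of satisfaction". The same sentence adds "side effects, via the Oxford-VR Side Effects Scale", so collector and time point are the same for both scales. No other use of either scale is mentioned.

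Two other sections show who this person is. Under The VR psychological treatment: "The treatment is supported by a staff member over six sessions". There the staff member introduces the software, helps set goals and tasks, and reviews progress. Under Randomisation, blinding and code-breaking: "The research assessors will be blinded to group allocation, but the patients and staff member present will not".

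Table 1 lists both measures as objectives; the side-effect row reads "Assess side effects of the VR therapy".

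The Adverse events section describes separate safety recording. It covers "any serious adverse events (SAE) reported to us", adds a check of every patient's medical notes once participation ends, and continues: "We will also record adverse events that are not serious". The non-serious category includes device effects of the VR treatment, software malfunction, and user error or misuse.

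**The concern.** A patient asked to rate a treatment through the person who supported them in it has a reason to be kind. The patients here are aged 16 to 30, were selected for low positive self-beliefs, and may have had up to six sessions with that person. The pull is towards higher satisfaction and fewer reported side effects.

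These two scales are the only instruments that the article names for the acceptability and side effects of a medical device. If they lean favourable, the description of Phoenix as well liked and well tolerated leans with them, and no later analysis can correct it. Unlike detail that an article may leave to a fuller protocol, the choice of collector is stated outright.

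**Working it through.** **1. Who collects, and what else would catch the same information**

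| Measure | Collected by | Stated time | Second route in the article |
|---|---|---|---|
| Satisfaction | Supporting staff member, unblinded | End of treatment | None |
| VR side effects | Supporting staff member, unblinded | End of treatment | Recording of non-serious events and device effects, not tied to end of treatment or to completers |

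The exposure is therefore uneven. Satisfaction rests wholly on the one route. Side effects have a second route, but no instrument or schedule is described for it, so it supplements a structured scale and does not replace it.

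**2. What cannot be calculated**

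The article gives no expected satisfaction score, side-effect rate or rate of stopping therapy. The size of any favourable lean in the answers cannot be derived.

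**3. Denominator**

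The only related figure is the sample size. Reproducing it (two-sided t-test, 5% level, 80% power, d = 0.67) gives 35.96, so 36 per arm and 72 in all; 72 / (1 − 0.10) = 80. It is correct and not in dispute. At 1:1 allocation the Phoenix arm has 80 / 2 = 40 patients.

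**4. Why the number rated should be reported (illustration on assumptions only)**

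Suppose that 10% of rated patients report a troublesome side effect, that m of the 40 are not rated, and that a proportion p of those m had one. Then

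whole-arm rate = [(40 − m) × 0.10 + m × p] / 40.

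| m | p = 10% | p = 30% | p = 50% |
|---|---|---|---|
| 0 | 10% | 10% | 10% |
| 4 | (3.6 + 0.4)/40 = 10% | (3.6 + 1.2)/40 = 12% | (3.6 + 2.0)/40 = 14% |
| 8 | (3.2 + 0.8)/40 = 10% | (3.2 + 2.4)/40 = 14% | (3.2 + 4.0)/40 = 18% |

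Against the 10% observed, the understatement is 0 to 4 points with 4 unrated and 0 to 8 points with 8 unrated. It is zero if everyone is rated or if the unrated do not differ. The extreme bounds, with none or all of the unrated affected, are 3.6/40 = 9% to 7.6/40 = 19% for m = 4, and 3.2/40 = 8% to 11.2/40 = 28% for m = 8. The table does not predict what will happen in this trial.

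**The case against.** The strongest reply has four parts.

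- **Blinding.** An assessor who asked about VR side effects would learn the allocation, so someone unblinded must collect these forms. This is inferred, since the article gives no reason, but it is sound. It justifies an unblinded collector. It does not require that the collector be the person supporting the therapy.
- **Mode of completion.** Collecting a form is not the same as interviewing. Patients may already fill it in privately and hand it over. The article does not say. A reader might infer that both results will certainly look better than they are; the text supports only a risk.
- **Early stoppers.** A reader might also infer that patients who stop because of side effects or dislike go unrated. The article does not say so. The Introduction describes six sessions as a maximum, so end of treatment can include the point of stopping, and form timing is detail that a fuller protocol may hold. The Analysis section keeps available data from therapy non-completers in the primary analyses. The 10% attrition figure there is loss to the trial, not stopping of therapy, and says nothing on this point.
- **Safety recording.** It would be wrong to read the device's safety case as resting on this one scale. The Adverse events section records non-serious events and device effects, and serious events are also sought in every patient's notes, in both arms.

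These replies remove any claim of certain bias or of a documented loss of early stoppers, and they soften the side-effect concern. They do not touch the satisfaction ratings, which have no second route.

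**Conclusion.** The point stands as a risk of favourable ratings on two descriptive measures taken in the Phoenix arm only. It is strongest for satisfaction and partly offset for side effects by adverse event recording. It rests on one natural reading: that the staff member named in the Assessments section is the one who supports the six sessions.

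No size can be given from the document, and zero bias is possible. The primary outcome, the power calculation and every between-arm comparison are unaffected. The Aims and hypotheses section also places both measures outside the primary and secondary hypotheses. This is an inexpensive improvement to the reporting of acceptability and tolerability, and it does not threaten the trial's main conclusion.

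**What to change.** Keep both scales and change three things:

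1. Patients complete them privately, by online link or sealed form, returned to an unblinded member of the trial team who takes no part in delivering the therapy. The blinded assessors do not see them.
2. Collect them at the last treatment contact, stating that this includes patients who stop early.
3. Report the number rated out of all patients allocated to Phoenix (40 if allocation is exactly equal), so that the reader can see how much is missing.

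No new instrument is needed. The cost is a different return route, possibly a few more missing forms, and a little time to chase them. The article does not say who on the team could take this on, so the task should be assigned by role.
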